### Strengthening Village Health Sanitation and Nutrition Committees (VHSNCs)

In intervention and control areas, activities are undertaken to strengthen the capacity of VHSNCs, which are village-level government-mandated bodies. VHSNCs are responsible for assessing the health needs of their community, preparing and implementing village health plans and monitoring the delivery of local health and nutrition services. During the study, several participatory meetings will be held with VHSNCs. These meetings will primarily aim to sensitise VHSNCs on issues related to inequity and exclusion in service provision, in addition to identifying and addressing gaps in health and nutrition services within their community.

### Measurement of health outcomes/effectiveness

#### Primary outcome

The primary outcome of the CARING trial is children's length-for-age z-scores.^17^ The trial was powered to detect a 0.15 SD difference in LAZ between intervention and control at the 0.05 significance level. A greater sample size would be required to detect a realistic change in the prevalence of stunting: our sample size allows us to detect a 13% reduction in stunting prevalence, which is an unfeasible effect for a 24 months intervention without food supplementation. Cost-effectiveness analyses focusing on cases of stunting averted would be useful to inform policymakers' decisions. We therefore propose to conduct a cost-effectiveness analysis for cases of stunting averted if there is evidence of impact on the prevalence of stunting in children at 18 months at the 0.1 significance level or below. Using these z-scores, we will calculate the prevalence of stunting among children at 18 months and calculate the number of cases of stunting averted. Cases averted will be calculated as the difference between the expected and the actual number of cases using the adjusted OR.

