In the India and Peru studies, cost-effectiveness analyses were conducted from the societal perspective. The India and Peru studies reported incremental cost-effectiveness ratios (ICERs) per case of stunting averted of $34.67^i^ and $55.16, respectively. The Peru study reported the cost per death averted at $1952. In Pakistan and Malawi, cost-effectiveness analyses were conducted from the provider perspective and as such their findings cannot be compared directly with the other two studies. They did, however, report a cost per disability-adjusted life year (DALY) averted of $12.20 and $42, respectively, which can then be compared with other ‘DALY averting’ interventions. In addition, the Pakistan study reported a cost per death averted of $406.

The proposed economic valuation of the CARING trial will be the first to assess the cost-effectiveness of combining participatory women's groups with home visits to reduce stunting. This economic evaluation will also employ a societal perspective, thus adding significantly to our understanding of the cost-effectiveness of this intervention and the likely fiscal space needed for its wider implementation. ICERs will be reported for cases of stunting averted, deaths averted and DALYs averted, in order to maximise comparability with other trials and ensure the usefulness of the economic evaluation as a resource allocation tool.

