#### Secondary outcomes

The trial has a number of secondary outcomes described in detail in the trial protocol.^17^ Cost-effectiveness analyses will be conducted for any reduction in three key secondary outcomes—underweight, wasting and infant mortality—where a significant impact on these outcomes is observed at the 0.1 level.

ICERs will thus be calculated for wasting, underweight and infant mortality, if a significant effect is observed at a p value of 0.1 or less. Estimates of life years saved will be calculated for infant mortality averted by the intervention if a significant finding is observed. Although no agreed DALY weight currently exists for undernutrition in any form, expected ‘DALYs averted’ will be modelled using mortality averted by the intervention if significant, and evidence from the wider literature about morbidity gains from averting stunting, wasting and underweight in young children.^31^

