### Cost-effectiveness analysis

The cost-effectiveness analysis will be conducted as a within-trial analysis using the intention-to-treat results, and will be presented in terms of ICERs, calculated as the arithmetic mean difference in cost between the community intervention combined with VHNSC strengthening versus VHNSC strengthening only, divided by the arithmetic mean difference in effect.^37^
^44^

ICERs will be calculated for the primary outcome measure, that is, cases of stunting prevented, and for selected secondary outcomes and summary measures, including cases of wasting and underweight prevented, cases of infant mortality averted, life years saved and DALYs averted.

A number of sensitivity analyses will be carried out in order to assess the impact on the cost-effectiveness results, of changes in variables and parameters with the greatest uncertainty or with the greatest impact on the total costs. Cost-effectiveness acceptability curves will be generated to further describe uncertainty around the cost estimates.^45^

Costs will be presented in 2016 prices in Indian rupees and International Dollars (INT$). All costs will be adjusted for inflation using the Indian Consumer Price Index (CPI) and will be converted to 2016 INT$ using the 2016 Purchasing Power Parity (PPP) conversion factor for India. Moreover, costs and outcomes will be converted to present values using an annual discount rate of 3% in the base case, and annual rates of 0% and 6% in sensitivity analysis.

The affordability of the intervention will be explored using a range of criteria, including the WHO-CHOICE criteria,^46^ together with an analysis of fiscal space for programme delivery using a generalised fiscal space assessment method^47^
^48^ and probabilistic analyses to determine a set of cost-effectiveness thresholds.^45^
^49^ These analyses will also enable the exploration of a multicriteria decision analysis framework for resource allocation to this and other similar interventions to reduce stunting and wasting in young children.^50^ A wide range of affordability measures have been selected, in part, due to the paucity of evidence on the cost-effectiveness of comparable interventions. This precludes the use of simpler league tables and requires a wider range of affordability measures against which subsequent analysts may compare their own findings.

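### The ICERs for stunting, wasting, underweight and infant mortality are calculated only if p is 0.1 or less, although other sections promise them without condition; the rule leaves an ICER missing or tilts it towards looking favourable

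*Protocol article*

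**What the plan says.** **Conditional statements.** The Primary outcome section proposes a "cost-effectiveness analysis for cases of stunting averted if there is evidence of impact on the prevalence of stunting" and sets the test on the "prevalence of stunting in children at 18 months at the 0.1 significance level or below". Just before this, it says that a realistic change in stunting would need a larger sample, and that the 13% reduction the trial can detect is not feasible for this intervention. Secondary outcomes continues: "ICERs will thus be calculated for wasting, underweight and infant mortality, if a significant effect is observed at a p value of 0.1 or less". It makes life years saved depend on a significant mortality finding, and DALYs averted are to be "modelled using mortality averted by the intervention if significant", together with morbidity gains taken from the literature. The morbidity part has no express condition.

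**Unconditional statements.** The background section on economic evaluations says "ICERs will be reported for cases of stunting averted, deaths averted and DALYs averted". The Cost-effectiveness analysis section says "ICERs will be calculated for the primary outcome measure, that is, cases of stunting prevented", and goes on to list wasting, underweight, infant mortality, life years and DALYs. The abstract gives a similar list without underweight. None of the three mentions a significance condition or refers back to the outcome sections.

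**Definition and uncertainty.** The Cost-effectiveness analysis section defines the ICER as the difference in arithmetic mean cost divided by the difference in arithmetic mean effect, by intention to treat. It plans sensitivity analyses, and acceptability curves to "further describe uncertainty around the cost estimates". The article does not say what is reported if no outcome meets the threshold.

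**The concern.** A significance test is not part of the ICER as the article defines it. Making the ICER depend on one has two consequences.

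- **A missing result.** If the intervention has a modest real effect and p exceeds 0.1, no cost per case or per death averted is produced, even though the estimate and its uncertainty would inform a decision. The article says the trial is too small for a realistic change in stunting, and then makes the stunting ICER depend on that test. The outcome the trial is powered for, length-for-age z-score, has no ICER planned as a fallback.
- **A selected result.** If the threshold is met, the effect in the denominator has been selected for being large, so cost per case averted tends to look too low. For DALYs, the mortality component moves from left out to fully counted as p crosses the threshold.

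The conflicting sections also mean that two analysts following this article could produce different sets of results.

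**Working it through.** **The plan's own figure.** The article states a detectable 13% reduction in stunting. It gives neither the power nor the ICC, and does not say whether 13% is relative or absolute, so the figure can be neither reproduced nor contradicted. With 1,260 per arm and two-sided 5% significance, 80% power for 13% allows a design effect of 1.13–1.64 if relative (base prevalence 45–55%), or about 5.5–5.8 if absolute.

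**Inputs**
- Sample: n = 2520 in 120 clusters (Trial design). This gives 21 per cluster and, assuming an equal split, 1,260 per arm.
- Prevalence: 47.5%, assumed. It is midway between the state figures of over 45% and over 50% (Study setting).
- ICC: 0.02 to 0.04, assumed.
- Threshold: p ≤ 0.1, assumed two-sided, so a favourable result needs z > 1.645.

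**Standard error**

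SE = √[2 × 0.475 × 0.525 / 1260 × (1 + 20 × ICC)]
- ICC 0.02 (design effect 1.4): SE = 2.35 points; smallest reduction that passes = 1.645 × 2.35 = 3.9 points.
- ICC 0.04 (design effect 1.8): SE = 2.67 points; smallest reduction that passes = 1.645 × 2.67 = 4.4 points.

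**Probability of passing, and mean estimate given passing**

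Let m = true reduction / SE. Then P(pass) = 1 − Φ(1.645 − m), and the mean passing estimate is SE × [m + φ(1.645 − m) / P(pass)]. For a true 3 points at ICC 0.02: m = 1.274, P = 0.356, mean = 5.47 points, ratio = 5.47 / 3 = 1.82.

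| True reduction (points) | Passes | Passing estimate too large by |
|---|---|---|
| 2 | 19–21% | 2.6–2.9 times |
| 3 | 30–36% | 1.8–2.0 times |
| 4 | 44–52% | 1.45–1.6 times |
| 6 | 73–82% | 1.13–1.20 times |

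The effect is the denominator. At a true 3 points, the ICER evaluated at the mean passing effect is therefore 1/2.0 to 1/1.8 of its true value, about half.

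**Where the powered effect lies.** The trial is powered for 0.15 SD in length-for-age z-score. Under a normal distribution with SD 1 and 47.5% stunted, a 0.15 shift lowers stunting by 0.475 − Φ(−0.063 − 0.15) = 0.059, about 6 points. That is the bottom row of the table.

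**A second route without ICC or prevalence.** Taking the SE as 13% / (1.96 + z for power), with 80–90% power assumed:
- A true effect of half the 13% passes 40–49% of the time and is overstated 1.5–1.7 times.
- A quarter of it passes 17–20% of the time and is overstated 2.7–3.1 times.
- The full 13% passes 88–95% of the time and is overstated 1.04–1.08 times.

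These proportions hold whether 13% is relative or absolute. The reading does matter for a fall of about 6 points: it passes 76–95% of the time if 13% is relative, and 35–44% if absolute.

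**The case against.** The rule is stated openly, fixed in advance and looser than 0.05. The outcome sections are the specific text, the abstract and background are summaries, and the analysis section speaks only of selected secondary outcomes, so the conflict could be settled by a cross-reference. That is fair on the drafting. But the analysis section does not qualify the stunting ICER at all, and fixing a selective rule in advance does not remove the selection.

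A reader might also infer stronger claims, which the document does not support:
- **That every ICER is conditional.** The morbidity part of DALYs is not expressly conditional, although it would probably draw on cases averted.
- **That failure leaves no economic result.** Total and incremental costs, and the fiscal-space analysis, carry no significance condition.
- **That the threshold will usually be missed.** This holds for true reductions of 2 or 3 points. At about 6 points it is usually met under the assumed ICCs, and the bias is modest. The article's remark on feasibility points to smaller effects but names none.
- **That four outcomes give a 34% chance of a spurious ICER.** This figure (1 − 0.9⁴) assumes independence and counts harms. Stunting, wasting and underweight are measured on the same children, and the secondary analyses are for reductions. The favourable-direction figure under independence is 1 − 0.95⁴ = 19%, and positive correlation lowers it.
- **That the acceptability curves will ignore effect uncertainty.** This rests on one loosely worded sentence, and the same section also mentions probabilistic analyses. The wording needs correcting, but it does not show that effects will be held fixed.

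**Conclusion.** The point holds in this form. The article makes the stunting, wasting, underweight and infant-mortality ICERs depend on p ≤ 0.1, and life years and the mortality part of DALYs depend on significance, while other sections promise ICERs for these outcomes without condition. Followed as written, the rule leaves an ICER missing or biases it towards looking favourable.

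The direction of the bias is certain, but its size depends on the true effect. It is about two- to threefold for true reductions of 2–3 points, and 13–20% for 6 points. These sizes rest on the assumed equal split, prevalence, ICC and two-sided test. The contradiction between sections, and the mismatch with the article's own definition of the ICER, rest on no assumption.

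**What to change.** 1. Delete the significance conditions under Primary outcome and Secondary outcomes.
2. Report incremental cost, incremental effect and the ICER for all named outcomes whatever the p value.
3. Always carry the estimated mortality difference, with its uncertainty, into life years and DALYs.
4. Show joint uncertainty in costs and effects on the cost-effectiveness plane and in acceptability curves, with a method that respects clustering.
5. In the Cost-effectiveness analysis section, reword the sentence on acceptability curves so that it covers uncertainty in costs and effects.

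The cost is rewording and a little extra analysis. The drawback is that some ICERs will have wide or undefined intervals where the effect is close to zero. For those, the plane and the acceptability curve should carry the interpretation.

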## Background

### Burden of child undernutrition

Undernutrition affects an estimated 165 million children globally and contributes to an estimated 45% of all child deaths worldwide.^1^ Stunting, that is, low length-for-age or height-for-age in young children, is a marker of chronic undernutrition. It is the result of multiple determinants, including long-term consumption of a low-quality diet in combination with morbidity, infectious diseases and environmental risks.^2–4^

Stunting in early childhood is associated with subsequent adverse consequences, including poor cognitive and educational performance, reduced work capacity and lower wages in adulthood.^5^ It also contributes to the intergenerational transmission of poverty.^6^ It is estimated that individual productivity losses attributable to undernutrition are more than 10% of lifetime earnings, and losses to gross domestic product (GDP) may be as high as 2–3% (World Bank, 2006). The burden of undernutrition disproportionately affects the most vulnerable populations in low and middle income countries (LMICs).^7^
^8^ The WHO has set a global target to reduce stunting by 40% by 2025,^9^ while the 2014 Global Nutrition Report emphasises the importance of nutrition as the foundation on which healthy lives, ‘resilient livelihoods’ and ‘thriving economies’ are built.^10^

Approximately one-third of the world's stunted children live in India. Stunting in India is most prevalent among the poorest households, Scheduled Tribes (ST) and Scheduled Caste (SC) communities.^11^
^12^ The Government of India has targeted undernutrition through the Integrated Child Development Scheme (ICDS) and the National Rural Health Mission (NRHM). The ICDS distributes supplementary food to children through a network of village-based workers known as ‘Anganwadi’ workers. Launched in 2005, the NRHM (now renamed National Health Mission or NHM) aims to provide accessible, affordable and quality healthcare services to the rural population and vulnerable groups.^13^ Although ICDS services have nationwide coverage, they mainly target children aged 3–6 years, by which time many of the adverse effects of early childhood undernutrition may already be established.

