### CARING trial

CARING is a cluster-randomised controlled trial (cRCT) located in two districts of Jharkhand and Odisha, eastern India. The trial aims to assess the effectiveness of a complex public health intervention that mirrors the proposed government reforms described above. The intervention involves recruiting and training a new community-based health worker engaged in improving feeding, infection control and caregiving practices for children under 2 years of age through monthly home visits to all children under 2. This new community-based worker also supports monthly women's groups meetings working through a ‘undernutrition-focused’ participatory learning and action cycle. The participatory learning and action cycle involves monthly group meetings for women. The new community-based health worker facilitates the meetings and a problem-solving approach is used to help groups identify community-level health and nutrition problems, and find locally feasible strategies to address the problems identified.

The trial aims to establish whether the intervention is effective and cost-effective in reducing stunting in children under 2, morbidity and mortality, when compared with current practice. In all study areas, we also attempt to strengthen Village Health Sanitation and Nutrition Committees (VHNSCs) as a common benefit to intervention and control clusters.

The CARING trial is described in detail elsewhere.^17^ The purpose of this article is to fully describe the methodology for the economic evaluation of the trial.

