### Study setting

As described fully in the trial protocol,^17^ the CARING trial takes place in West Singhbhum (Jharkhand state) and Kendujhar (Odisha state) districts in India. Odisha and Jharkhand are among the poorest states in India, with high rates of child mortality and undernutrition,^25^
^26^ and female literacy rates below 50%.^27^ In 2010, under-5 mortality was estimated 61 and 83 per 1000 live births in rural Jharkhand and Odisha, respectively.^28^
^29^ In Jharkhand over 50% of children are stunted, and in Odisha over 45% are stunted.^25^
^26^ The study districts are predominantly rural, with a combined total population of ∼3.3 million.^17^

Community-based health and nutrition services for mothers and children in the study villages are provided by three community workers: an Anganwadi worker (AWW), an Accredited Social Health Activist (ASHA) and an Auxiliary Nurse Midwife (ANM). AWWs provide supplementary nutrition to pregnant women, breastfeeding mothers and children aged 6 months to 6 years. ASHAs support community members in accessing essential healthcare services and promote institutional deliveries. ANMs provide services such as childhood immunisation and essential medicines. Community-based services are supplemented with care from primary care centres, MTCs that specialise in the treatment of SAM and hospitals.

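### The stunting ICER counts only children alive and measured at 18 months, so a survival gain among frailer children would modestly understate stunting cases averted, and other planned ICERs may not credit that gain

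*Protocol article*

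**What the plan says.** The Primary outcome section fixes how the effect side of the stunting ICER is counted. From the length-for-age z-scores, "we will calculate the prevalence of stunting among children at 18 months and calculate the number of cases of stunting averted". The rule follows: "Cases averted will be calculated as the difference between the expected and the actual number of cases", and these come from the adjusted odds ratio. The stunting ICER is produced only "if there is evidence of impact on the prevalence of stunting in children at 18 months at the 0.1 significance level or below".

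The Study population section enrols women in the third trimester and follows mother and child for 18 months after birth. Under CARING trial, the stated aim is to learn whether the intervention is "effective and cost-effective in reducing stunting in children under 2, morbidity and mortality, when compared with current practice". The Burden of child undernutrition section says undernutrition "contributes to an estimated 45% of all child deaths worldwide". The Study setting section adds that "under-5 mortality was estimated 61 and 83 per 1000 live births in rural Jharkhand and Odisha, respectively".

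Deaths enter elsewhere. The Secondary outcomes section plans an infant mortality ICER, life years saved and a mortality component in DALYs, each only if the mortality effect is significant at 0.1. The Cost-effectiveness analysis section lists stunting cases prevented first among the ICERs. Nothing in the article links the stunting count to deaths before 18 months.

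**The concern.** Length at 18 months exists only for children who are alive and measured, and survival to that visit happens after randomisation and is itself a target of the intervention. If the intervention keeps alive children who would have died under control conditions, those children join the intervention arm's stunting denominator with no counterpart in the control arm. If they are stunted more often than other survivors, they raise intervention-arm prevalence, pull the odds ratio towards 1 and reduce the cases averted. The same shift enters the test that decides whether the stunting ICER is calculated at all.

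A payer looking at the stunting ratio could not tell whether a weak result partly reflects lives saved. The separate mortality results would help only if they were reliably reported, and they depend on a significance test. Wasting and underweight share the problem if they are measured at the same visit, which the article does not state.

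**Working it through.** **The article's own figure.** The only effect size given for stunting is a 13% detectable reduction. Power and intracluster correlation are not in the article, so it cannot be reproduced exactly. A 0.15 SD difference needs 698 children per arm (80% power) or 934 (90% power) before clustering. At either effective size, with its matching power, the detectable stunting difference is about 7.5 percentage points: 15% relative at 50% prevalence, 13.6% at 55% and 12.4% at 60%. I therefore read 13% as relative. The figure is not disputed here. The article itself calls an effect of that size unfeasible, so 5% is also shown.

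**Inputs.**
- p, control stunting: 0.45–0.50 (Study setting gives over 45% and over 50%).
- m, death by 18 months: 0.06, an assumption. The article gives only under-5 mortality, 61 and 83 per 1000, which is an upper proxy.
- r, relative cut in mortality: 0.2–0.3, an assumption.
- s, stunting among saved children: 0.5–0.8, an assumption.
- d, relative stunting reduction in children who would survive in either arm: 0.13 or 0.05.

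**Formulas, per birth.** I take expected cases as intervention-arm survivors times control prevalence.
- Expected = (1 − m + m·r)·p
- Actual = (1 − m)·p·(1 − d) + m·r·s
- Expected − actual = (1 − m)·p·d − m·r·(s − p)

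The first term is the number truly averted and the second is the understatement.

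**Results per 1000 births.**
- Saved children: 1000 × 0.06 × 0.2 = 12, up to 1000 × 0.06 × 0.3 = 18.
- Understatement: from 12 × (0.50 − 0.50) = 0 to 18 × (0.80 − 0.45) = 6.3.
- Truly averted at d = 0.13: 940 × 0.45 × 0.13 = 55.0 to 940 × 0.50 × 0.13 = 61.1. Share lost: 0 to 6.3/55.0 = 11%.
- Truly averted at d = 0.05: 940 × 0.45 × 0.05 = 21.2 to 940 × 0.50 × 0.05 = 23.5. Share lost: 0 to 6.3/21.15 = 30%.

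**Cross-check on the trial's size.** With 2520 children split evenly, there are 1260 per arm. Using 61–83 deaths per 1000 and an assumed mortality ratio of 0.7–0.9, between 1260 × 0.061 × 0.1 = 8 and 1260 × 0.083 × 0.3 = 31 children are saved. At 70% stunted the count falls by 1.5 to 7.8 cases. If all were stunted it falls by 3.8 to 17.3. A 13% reduction averts about 69–76 cases per arm and a 5% reduction about 26–29 (at about 93% survival).

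**Does the mortality ICER cover the gap?** With 1260 per arm, mortality of 60 per 1000 and no loss for clustering, power at two-sided 0.1 is:
- 20% cut (0.060 v 0.048): z = 0.012/0.0090 = 1.33; Φ(1.33 − 1.645) = 38%.
- 30% cut (0.060 v 0.042): z = 0.018/0.00876 = 2.06; Φ(2.06 − 1.645) = 66%.

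Clustering, and deaths counted only in infancy, would lower both. A real survival gain therefore has a substantial chance of receiving no credit.

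**What a composite adds.** The gain in children alive and not stunted is (1 − m)·p·d + m·r·(1 − s). It exceeds the odds-ratio count by m·r·(1 − p), whatever s is: 12 × 0.50 = 6.0 to 18 × 0.55 = 9.9 per 1000 births. This difference follows from the definition; it is the survival credit missing from the stunting ICER and not evidence of bias.

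**The case against.** **Stronger readings a reader might infer.** One is that every saved stunted child costs the programme a full case and that a death is scored as a non-stunted child. That would hold if raw counts per birth were compared, with a loss of m·r·s, or 6–14 per 1000. The stated rule uses prevalence and an adjusted odds ratio, so a death leaves numerator and denominator alike. A saved stunted child then costs 1 − p, about half a case, and a saved non-stunted child gives back p. Another inference is that the stunting ICER necessarily worsens as more deaths are prevented. That is so only if saved children are stunted more often than other survivors. The share of child deaths linked to undernutrition makes this direction plausible, but the article does not quantify it.

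**The 5% scenario often yields no ICER.** This is fair. Assuming 50% control stunting, 80–90% power for 0.15 SD and no attrition, a true 5% reduction passes the 0.1 gate about 24–29% of the time. The 30% upper end should be read with that in mind.

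**Mortality is already analysed.** It is, and DALYs combine mortality with morbidity. But each credits survival only at p ≤ 0.1, and none changes the stunting ratio.

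**The composite is a value judgement.** This stands. It treats a death and a stunted survivor as equal failures, and replacing the stunting ICER with it would conflict with the stated wish for comparability with other trials. It belongs beside the planned ICER.

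**The main trial protocol is not shown.** It may say how deaths are handled in the anthropometry. The economic counting rule is nevertheless fixed in this article.

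**Conclusion.** The point holds as a modest, conditional one. The stunting ICER describes survivors at 18 months and is not labelled so. Under the assumptions listed, the understatement lies between nothing and about 6 cases per 1000 births: small against a 13% reduction (at most 11%) and potentially material against 5% (at most 30%). The lower bound is zero, reached when saved children are stunted at the background rate. The size rests on three quantities the article does not give: mortality to 18 months, the effect on it, and stunting among saved children. The 0.1 gate on mortality means the other ICERs cannot be relied on to make up the difference. This is a cheap improvement and does not invalidate the planned analysis.

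**What to change.** In the Primary outcome and Cost-effectiveness analysis sections:
- Keep cost per stunting case averted as planned, and label it as among survivors at 18 months.
- Report beside it, as a prespecified sensitivity ICER, the cost per additional child alive and not stunted at 18 months, with all live births in the recruited cohort as denominator and death counted as failure.
- Do the same for wasting and underweight if they are measured at that visit.

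The cost is one further outcome definition. It uses vital status and length, both needed for outcomes already planned, and requires no new participants. The downside is the equal weighting of a death and a stunted survivor, and the lack of comparability with earlier cost-per-stunting-case figures. For those reasons it supplements the planned ICER and does not replace it.

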### Trial design

In the CARING trial, a total of 120 purposively selected geographical clusters, with an estimated total population of 121 531, were randomised to the two trial arms. The 60 clusters in the intervention arm received home visits, participatory learning and action meetings and support to VHNSCs as described further below. The 60 clusters in the control arm received only the support to VHNSCs. Study participants are pregnant women identified in the third trimester of pregnancy and their children (n=2520). The randomisation, which took place in July 2013, was stratified by district and by number of hamlets per cluster. The trial is ongoing and is due to finish in 2016.

In the intervention clusters, a community intervention to improve children's growth involving home visits to all children under 2 and monthly participatory learning and action meetings with women's groups, combined with VHSNC strengthening activities, is being implemented. In the control clusters, only VHSNC strengthening is implemented. In the following section, we present a brief description of the intervention strategies. A full description of the intervention design within the CARING trial is described in detail elsewhere.^17^

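### Cases of stunting averted are to come from the adjusted odds ratio with no stated conversion to risk, so the ICER denominator is left open by up to about twofold

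*Protocol article*

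**What the plan says.** The Primary outcome section says that the prevalence of stunting at 18 months will be worked out from the z-scores, and then gives the rule for the effect: "Cases averted will be calculated as the difference between the expected and the actual number of cases using the adjusted OR". It gives no formula for the expected number and does not say whether the adjusted OR is marginal or conditional on covariates or clusters. The stunting ICER is to be calculated only "if there is evidence of impact on the prevalence of stunting in children at 18 months at the 0.1 significance level or below".

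The Cost-effectiveness analysis section defines every ICER as the arithmetic mean cost difference between arms "divided by the arithmetic mean difference in effect". It mentions neither the OR nor adjustment.

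On how common the outcome is, the Study setting section says: "In Jharkhand over 50% of children are stunted, and in Odisha over 45% are stunted".

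**The concern.** An OR approximates a risk ratio only when the outcome is rare. Here about half the children may be stunted, so the two are far apart, and an OR does not translate into a number of cases without an explicit step from odds to risk. The rule leaves that step out. An analyst could divide the actual cases by the OR, multiply expected cases by one minus the OR, or convert through the odds to risks. Only the last gives a risk difference.

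Cases averted is the denominator of the ICER that the article presents as its main result. Both shortcuts err in the same direction: they inflate the denominator and make the intervention look cheaper per case. For scale, the two societal-perspective stunting ICERs cited in the background, $34.67 and $55.16, differ by a factor of 55.16/34.67 = 1.59, which is within the range at issue here. Under the division shortcut the error also grows with baseline risk. It would therefore not be constant across the socioeconomic strata planned in the Equity impact section.

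**Working it through.** **Inputs.**
- Control risk p0: 0.45 and 0.50, from the state prevalences in Study setting. These are an assumed proxy for control-arm risk at 18 months, which the article does not give.
- OR: 0.7 to 0.9. This is an assumption, since the article states no OR.
- Children per arm: 1260, assumed as half of the 2520 in Trial design. It affects counts only, not percentages.
- Illustrative effect: the article's own figure, "our sample size allows us to detect a 13% reduction in stunting prevalence".

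**The article's own figure.** The 13% cannot be reproduced, because power, intracluster correlation and baseline risk are not given, nor whether it is relative or absolute. A plausibility check uses the usual two-proportion formula, two-sided 0.05 and 80% power:

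n per arm = [1.96 × √(2·p̄·(1−p̄)) + 0.842 × √(p0(1−p0) + p1(1−p1))]² / (p0−p1)²

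- 13% relative: 1117 per arm at p0 = 0.45 and 924 at p0 = 0.50, so 1260 per arm leaves room for design effects of 1.13 and 1.36.
- 13 points absolute: 219 and 228 per arm, implying design effects of 5.75 and 5.53.

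The relative reading is the more plausible and is used below for illustration. The finding does not depend on it.

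**Step 1: formulas.** For a marginal OR, p1 = OR·p0 / (1−p0+OR·p0), so the true risk difference is

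RD = p0 − p1 = p0(1−p0)(1−OR) / (1−p0+OR·p0).

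- Reading A, expected = actual/OR: averted risk = p1/OR − p1. Ratio to RD = 1/(1−p0), whatever the OR.
- Reading B, (1−OR) × expected cases: averted risk = (1−OR)·p0. Ratio to RD = (1−p0+OR·p0)/(1−p0).
- Reading C, conversion through odds: o = [p1/(1−p1)]/OR, expected risk = o/(1+o) = p0. Ratio to RD = 1.

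**Step 2: percentage points averted at OR = 0.80.**

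| p0 | p1 | True RD (= C) | B | A |
|---|---|---|---|---|
| 0.50 | 0.40/0.90 = 0.4444 | 5.56 | 10.0 (1.80-fold) | 11.1 (2.00-fold) |
| 0.45 | 0.36/0.91 = 0.3956 | 5.44 | 9.0 (1.65-fold) | 9.9 (1.82-fold) |

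Over OR 0.7 to 0.9 and p0 0.45 to 0.50:
- B runs from 0.865/0.55 = 1.57 to 0.95/0.50 = 1.90.
- A runs from 1/0.55 = 1.82 to 1/0.50 = 2.00.
- The ICER would be between 1/2.00 = 50% and 1/1.57 = 64% of its proper value.

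**Step 3: case counts, 13% relative reduction, 1260 children.**

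| p0 | p1 | OR | True (= C) | B | A |
|---|---|---|---|---|---|
| 0.50 | 0.435 | 0.770 | 81.9 | 145.0 (+77%) | 163.8 (+100%) |
| 0.45 | 0.3915 | 0.786 | 73.7 | 121.1 (+64%) | 134.0 (+82%) |

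The article itself regards this effect as out of reach. With a smaller effect, B moves towards A: for a 5-point fall, B is +82% at p0 = 0.50 and +67% at p0 = 0.45.

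**Step 4: if the adjusted OR is conditional.** Assume normal between-child variation on the logit scale with standard deviation s. Find the intercepts that give average risks of 0.50 and 0.435, take the conditional OR from their difference, and apply reading C to the average risk. For s = 1.0 the conditional OR is 0.729, against a marginal 0.770. Then o = 0.770/0.729 = 1.056, expected risk = 0.514, and averted risk = 0.079 against a true 0.065. Overstatement:
- s = 0.3: 2.2%
- s = 0.5: 5.9%
- s = 0.8: 14.2%
- s = 1.0: 21.0%

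The values of s are assumptions.

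**The case against.** The strongest reply is that the article never says case counts will be scaled by the OR. An expected number can be obtained through the odds, and for a marginal OR that returns the true figure exactly (reading C). The observed prevalences will be in hand, so no outside baseline risk is needed. The article is also condensed, and a conversion formula is commonly left to an analysis plan.

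Most of this stands, and it rules out three stronger readings.

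- A reader might infer that the plan will overstate cases averted by 60 to 100%. The text does not support that; the error arises only under readings A or B.
- A reader might infer that the two sections contradict each other. They do not. A risk difference derived from an adjusted OR fits the ICER definition; the sections are merely not connected.
- A reader might extend the point to wasting, underweight and infant mortality. The Secondary outcomes section states no OR rule for them. For mortality the gap would be small anyway: at the quoted under-5 rates of 61 and 83 per 1000, 1/(1−p0) is 1.06 and 1.09.

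The appeal to a condensed article does not dispose of the point. The article sets out to give the full methods of the economic evaluation, and it does fix a rule here. That rule names an effect measure that does not map directly to cases and admits answers up to twofold apart. Conversion through the odds is also not a complete rescue if the adjusted OR is conditional (Step 4).

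**Conclusion.** The point holds as a badly fixed rule, not as a demonstrated error. The denominator of the stunting ICER is tied to an adjusted OR for a common outcome, the step from odds to risk is not given, and the rule is not reconciled with the ICER definition.

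The size depends on what the analyst does:
- about 57 to 100% overstatement of cases averted if counts are multiplied or divided by the OR;
- none if a marginal OR is correctly converted to risks;
- about 2 to 20% if a conditional OR is converted at the average risk.

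These figures rest on state prevalences standing in for control-arm risk at 18 months, on assumed ORs of 0.7 to 0.9, and, for the last item, on assumed between-child standard deviations of 0.3 to 1.0. A control risk above 50% would enlarge the first item: at 0.55, reading A gives 1/0.45 = 2.22-fold. The matter arises only if the 0.1 trigger for the stunting analysis is met. Because both shortcuts favour the intervention, the conversion should be settled before the effect estimate is seen.

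**What to change.** Replace the sentence in the Primary outcome section with wording such as: cases of stunting averted will equal the adjusted marginal risk difference in stunting at 18 months, with a cluster-robust confidence interval, multiplied by the number of children in the stated reference population. Name that population. The risk difference can come from standardised predictions under each arm from the cluster-adjusted model, or from an identity-link model that allows for clustering. Add that this quantity is the effect difference used in the stunting ICER, which ties the rule to the Cost-effectiveness analysis section. The adjusted OR may still be reported as a trial result.

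No new data are needed. The cost is slightly more analysis work and possibly a smaller number of cases averted, hence a less favourable ICER, than one of the shortcuts would give.
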